# Mobile Health–Supported Virtual Reality and Group Problem Management Plus: Protocol for a Cluster Randomized Trial Among Urban Refugee and Displaced Youth in Kampala, Uganda (Tushirikiane4MH, Supporting Each Other for Mental Health)

**DOI:** 10.2196/42342

**Published:** 2022-12-08

**Keywords:** adolescents and youth, mental health, refugee, implementation research, virtual reality, mobile health, Uganda, urban

## Abstract

**Background:**

Although mental health challenges disproportionately affect people in humanitarian contexts, most refugee youth do not receive the mental health support needed. Uganda is the largest refugee-hosting nation in Africa, hosting over 1.58 million refugees in 2022, with more than 111,000 living in the city of Kampala. There is limited information about effective and feasible interventions to improve mental health outcomes and mental health literacy, and to reduce mental health stigma among urban refugee adolescents and youth in low- and middle-income countries (LMICs). Virtual reality (VR) is a promising approach to reduce stigma and improve mental health and coping, yet such interventions have not yet been tested in LMICs where most forcibly displaced people reside. Group Problem Management Plus (GPM+) is a scalable brief psychological transdiagnostic intervention for people experiencing a range of adversities, but has not been tested with adolescents and youth to date. Further, mobile health (mHealth) strategies have demonstrated promise in promoting mental health literacy.

**Objective:**

The aim of this study is to evaluate the feasibility and effectiveness of two youth-tailored mental health interventions (VR alone and VR combined with GMP+) in comparison with the standard of care in improving mental health outcomes among refugee and displaced youth aged 16-24 years in Kampala, Uganda.

**Methods:**

A three-arm cluster randomized controlled trial will be implemented across five informal settlements grouped into three sites, based on proximity, and randomized in a 1:1:1 design. Approximately 330 adolescents (110 per cluster) are enrolled and will be followed for approximately 16 weeks. Data will be collected at three time points: baseline enrollment, 8 weeks following enrollment, and 16 weeks after enrollment. Primary (depression) and secondary outcomes (mental health literacy, attitudes toward mental help–seeking, adaptive coping, mental health stigma, mental well-being, level of functioning) will be evaluated.

**Results:**

The study will be conducted in accordance with CONSORT (Consolidated Standards of Reporting Trials) guidelines. The study has received ethical approval from the University of Toronto (#40965; May 12, 2021), Mildmay Uganda Research Ethics Committee (MUREC-2021-41; June 24, 2021), and Uganda National Council for Science & Technology (SS1021ES; January 1, 2022). A qualitative formative phase was conducted using focus groups and in-depth, semistructured key informant interviews to understand contextual factors influencing mental well-being among urban refugee and displaced youth. Qualitative findings will inform the VR intervention, SMS text check-in messages, and the adaptation of GPM+. Intervention development was conducted in collaboration with refugee youth peer navigators. The trial launched in June 2022 and the final follow-up survey will be conducted in November 2022.

**Conclusions:**

This study will contribute to the knowledge of youth-tailored mental health intervention strategies for urban refugee and displaced youth living in informal settlements in LMIC contexts. Findings will be shared in peer-reviewed publications, conference presentations, and with community dissemination.

**Trial Registration:**

ClinicalTrials.gov NCT05187689; https://clinicaltrials.gov/ct2/show/NCT05187689

**International Registered Report Identifier (IRRID):**

DERR1-10.2196/42342

## Introduction

At the end of 2021, there were 89.4 million forcibly displaced persons across the globe, 83% of whom were hosted in low- and middle-income countries (LMICs) and 41% were children and youth under 18 years old [1]. Mental health challenges such as depression and anxiety disproportionately affect persons in humanitarian contexts; yet, most forcibly displaced persons do not receive the mental health support needed [2,3]. Myriad stressors contribute to psychological distress among refugee and displaced youth, including trauma, violence, food insecurity, and social marginalization [2,4]. Chronic psychological stress among adolescents can have life-long harmful impacts on neurobiological systems that are connected with emotional and behavioral regulation [5]. It is therefore of particular importance to mitigate psychological distress and to promote mental well-being among refugee and displaced adolescents and youth.

Uganda is the largest refugee-hosting nation in Africa with over 1.5 million refugees in 2022 [6]. There are 118,000 urban refugees in Uganda who live in Kampala, 27% of whom are youth aged 15-24 years [7]. There is a trend of urbanization of refugees globally, with more than 60% of refugees and 80% of internally displaced persons globally living in urban regions [8]. Many urban refugees such as those in Kampala live in informal settlements, including slums [9-11]. Socioenvironmental stressors in slums and informal settlements—such as violence and poverty—may harm mental well-being, yet mental health interventions in these contexts have not centered on the needs and priorities of urban refugee and displaced youth [12]. Most studies on the health of refugee and displaced persons have focused on refugee settlement contexts, leaving knowledge gaps regarding efficacious strategies to improve mental health among urban refugees [11].

A systematic review of mental health and psychosocial support for children (7-18 years old) in humanitarian settings identified knowledge gaps regarding effective strategies to reduce depression and anxiety [3]. Strategies in Uganda included sports for development, which only resulted in positive effects for boys [13], and a creative play group, which only resulted in positive effects for girls [14]. A 2018 cross-sectional survey with urban refugee and displaced youth (N=445) aged 16-24 years in Kampala, Uganda, found that three-quarters (74%) of adolescent girls and young women, and nearly half (49%) of adolescent boys and young men reported depressive symptoms [4]. These alarming statistics highlight the need for concrete solutions developed with and for urban refugee youth to alleviate this distress and risk of depression. In July 2020, Uganda opened its borders to receive more refugees from the Democratic Republic of the Congo (DRC) in the midst of the COVID-19 pandemic [15]. While mental health risks may be heightened during pandemics such as COVID-19 [16], researchers identified a chronically high prevalence of depression among urban refugee youth in Kampala both before (27.5%) and after (28.9%) declaration of the pandemic in March 2020 [17], signaling the urgent need to address chronic depression among this population.

Two key mental health needs that are understudied among refugee youth in LMICs such as Uganda include mental health literacy and mental health stigma reduction. Mental health literacy comprises knowledge and understanding of (1) different types of mental health issues and distress, (2) mental health risks and underlying causes of mental health challenges, (3) self-help strategies for mental health, (4) accessible and available professional help, and (5) recognizing when to seek mental health support and how to access it [18]. Interventions to advance mental health literacy may result in help-seeking for depression, anxiety, and psychological distress; however, there is a need for rigorous evaluations of the benefits of mental health literacy programs in LMIC and humanitarian contexts [19]. Researchers have called for more mental health literacy interventions specifically in Africa [20]. Indeed, mental health literacy programs tailored for refugees have largely focused on adults and/or high-income contexts [21,22]. This is also true for mental health stigma reduction, with the only randomized controlled trial (RCT) identified with refugees having been conducted with adult refugee men in the high-income context of Australia [23]. A systematic review reported that no trials have focused on reducing mental health stigma in low-income countries [24]. This review also reported a range of efficacious approaches to reducing mental health stigma, including via advancing mental health literacy [24]. Another systematic review on mental health stigma reduction reported that educational interventions were effective in reducing stigma, and that there were no differences in effectiveness between online and face-to-face mental health stigma reduction [25].

Emerging evidence suggests that tailored virtual reality (VR) scenarios can contribute to improved mental health outcomes. For example, a recent systematic review documented the efficacy of VR in treating posttraumatic stress disorder [26]. Yet, all studies were focused on adults in high-income settings and most were conducted with veterans [26]. To our knowledge, VR has not been piloted with youth in LMIC or humanitarian settings. Another promising mental health intervention approach is Group Problem Management Plus (GPM+), a World Health Organization (WHO) scalable group-based brief psychological transdiagnostic intervention for persons experiencing a range of adversities [27]. Problem Management Plus, delivered to individuals, was associated with reduced psychological distress, anxiety, depression, personally identified problems, and posttraumatic stress in RCTs with Kenyan adults [28] and conflict-affected adults in Pakistan [29]. The group-based delivery format, GPM+, was feasible and acceptable among conflict-affected adults in Nepal [30] and Pakistan [31], and is currently being tested among adult refugees in Turkey [32] and Jordan [33]. The WHO states that this program is likely efficacious among adolescents aged 16 years and older [27]; however, GPM+ has not yet been evaluated with refugee adolescents and youth.

This paper provides the study protocol for the Tushirikiane (roughly translating to “Supporting Each Other” in Swahili) for Mental Health (Tushirikiane4MH) study that aims to address these knowledge gaps regarding efficacious mental health interventions with and for urban refugee and displaced youth in Kampala, Uganda. Specifically, Tushirikiane4MH will test the effectiveness and feasibility of a VR intervention on its own and the combination of VR and GPM+ compared with standard of care. The findings can be used to inform the implementation and scale-up of mental health interventions with urban refugee and displaced youth across Uganda and other humanitarian contexts.

This study aims to evaluate the feasibility of two youth-tailored mental health interventions: (1) a VR experience focused on mental health literacy and psychological first-aid [34] skills, supplemented with mobile health (mHealth) delivered via SMS-based bidirectional messages and information; and (2) GPM+ in combination with the VR experience. A third arm, the waitlist control arm, will receive the GPM+ intervention on its own after the first two interventions are complete. The primary study objective is to determine the effectiveness of the interventions on reducing depression [35]. Secondary objectives include examining the effectiveness of the interventions on (1) improving mental health literacy [36-38], (2) increasing adaptive coping strategies [39,40], (3) reducing mental health stigma [41], (4) increasing mental health well-being [42], and (5) improving level of functioning [43].

## Methods

### Study Design

To evaluate intervention effectiveness, we will conduct a cluster randomized controlled trial (cRCT), in which five informal settlements in Kampala will be randomized at a 1:1:1 ratio to one of the three study arms. Peer navigators, refugee youth living in the five informal settlements, are trained in research methods and ethics, and will enroll youth into the study following obtaining written informed consent. Youth will be assigned to the study arm corresponding to the informal settlement they live in. A cluster randomization approach was selected to mitigate challenges of experimental contamination, as youth living in slums and informal settlements have shared sociophysical environments [44], thus addressing internal validity threats, although we will collect individual-level outcome data. We will perform data collection at three time points: baseline enrollment, 8 weeks following implementation, and 16 weeks following implementation.

### Study Setting

This trial is being conducted in the Ugandan capital of Kampala in five informal settlements, grouped into three sites based on geographic proximity (1: Kabalagala and Kansanga, 2: Katwe and Nsambya, and 3: Rubaga). These settlements were purposively chosen because: (1) they host many refugee and displaced persons in Kampala [45-48], largely from the DRC, Rwanda, and Burundi [49]; (2) these communities share similarities in socioeconomic status and living conditions, health care access, and languages; and (3) prior research noted a high prevalence of depressive symptoms among urban refugee youth in these communities [4,17]. Full details regarding the trial site geography and population have been described elsewhere [50].

### Study Population and Eligibility Criteria

Approximately 330 youth (110 per cluster) aged 16-25 years will be enrolled into this study. Eligibility criteria for inclusion are: (1) currently living in one of the five selected informal settlements in Kampala (Kabalagala, Kansanga, Katwe, Nsambya, or Rubaga); (2) identifying as a refugee or displaced person, or having refugee or displaced parents; (3) aged 16-25 years; (4) owning or have daily access to a mobile phone; and (5) speaking French, English, Luganda, Kirundi, Kinyarwanda, or Swahili. Eligibility screening (via phone, in person, or WhatsApp) with interested participants will be conducted by trained peer navigators.

### Participant Recruitment and Retention

The project team includes a refugee youth–focused community-based nongovernmental organization with expertise on youth engagement and programs for refugee youth. The team also includes academics, community-based practitioners, and stakeholders from the Ugandan Ministry of Health. Peer navigators—refugee and displaced youth aged 18-24 years living in these same five informal settlements (Kabalagala, Kansanga, Katwe, Nsambya, or Rubaga)—will work with the study coordinator and implementing partners to facilitate participant recruitment, and will further participate in study design and pilot testing. The 12 peer navigators (6 young women, 6 young men) have experience working in the various study communities as health educators or peer educators. They were identified and recruited by community-based collaborators and are deeply respected and connected in their communities.

Participants will be recruited within each settlement using purposive methods, including word-of-mouth and venue-based sampling at refugee agencies and community events. Recruitment will begin with participants who belong to the Tushirkiane cohort with this same study team and participated in previous completed trials on HIV self-testing [50] and COVID-19 prevention [51]. There will be additional purposive recruitment of 16- and 17-year-old participants to refresh the cohort. To engage and retain participants, peer navigators employed multiple strategies, including SMS and WhatsApp reminders, and local community partners also facilitated maintaining connection with study participants through outreach events.

### Patient and Public Involvement in Research

Study collaborators at Young African Refugees for Integral Development (YARID), a well-established youth refugee nongovernmental organization in Kampala, have been involved in the research from the initial stage of developing the research question and focus. The study protocol was developed after a formative qualitative research phase (Phase 1), which included: (1) in-depth semistructured key informant interviews with professionals in various roles supporting the health and well-being of refugee youth in Uganda (n=10); and (2) age- and- gender-segregated focus groups (4 discussions with 6 people in each focus group; n=24 participants in total) with refugee youth in Kampala aged 16-24 years. One focus group discussion each was held with young women aged 16-19 years, young women aged 20-24 years, young men aged 16-19 years, and young men aged 20-24 years, respectively. This formative qualitative work explored refugee youth perspectives on mental health, mental health literacy, and mental health stigma. These qualitative findings were used to identify key themes for development of the VR scenario, SMS content, and to adapt GPM+ to this context and population group. In this way, the study responds to the mental health needs and priorities of urban refugee youth in this context.

### Intervention Description

#### Design

The study was designed as a three-arm cRCT consisting of two treatment arms and one control arm. Clusters will be randomized to one of three arms: (1) VR, (2) VR plus GPM+, or (3) waitlist control, followed by GPM+ after intervention implementation and follow-up. Data will be collected at baseline, after intervention implementation (8 weeks postintervention), and at follow-up (16 weeks postintervention). The third arm (waitlist control) will receive an additional survey 8 weeks following the intervention to evaluate outcome changes. The VR and GPM+ arms receive weekly SMS messages with mental health literacy information and bidirectional check-ins (“how are you?” messages) where they can access any needed peer support. All study members will receive YARID resources and referrals as needed for mental health support from a trained social worker. The trial arms and interventions are described below and summarized in Figure 1.

**Figure 1 figure1:**
[figure not shown]
Study design for Tushirikiane4MH, a cluster randomized controlled trial of mental health literacy and mental health promotion strategies among urban refugee and displaced youth in Kampala, Uganda. GPM+, Group Problem Management Plus; VR: virtual reality.

#### Arm 1: VR Alone

Participants in this arm will be enrolled into an immersive, interactive 15-minute VR session. The VR scenario was designed to address Phase 1 findings, and integrates mental health literacy [18], psychological first aid [34], and mindful self-compassion information and activities [52]. The VR space was designed to be visibly similar to the environment of informal settlements in Kampala, and will be offered in participants’ language of choice (French, English, Kirundi, Kinyarwanda, or Swahili). Participants will be invited to participate in the VR scenario in a private room or in an outdoor setting at the partner organization. The VR session will be viewed on low-cost VR headsets and the study equipment will be sanitized and cleaned between uses.

#### Arm 2: VR and GPM+

Participants in this arm will be enrolled into the VR intervention (as described above) as well as GPM+. GPM+ is a WHO brief psychological transdiagnostic intervention for persons experiencing a range of adversities, including poverty and war, that, over five group sessions, aims to address both practical (eg, housing) and emotional (eg, stress) challenges [27]. Sessions employ evidence-based approaches to stress management, problem-solving, behavioral activation, and social support to reduce a range of mental health concerns. The intervention includes five 3-hour sessions, each with a distinct mechanism of action, which are described in Table 1.

**Table 1 table1:** Group Problem Management Plus sessions and their mechanisms of action.

Session	Key mechanisms of action
Managing stress	Identifying goals, learning deep breathing and techniques for stress management
Managing problems	Identifying one solvable and practical problem, brainstorming possible solutions together
Get going, keep doing	Learning about depression and inactivity, and identifying and planning small enjoyable activities
Strengthening social support	Discussing a range of social support resources and making plans to increase social support
Staying well	Reviewing all of the mechanisms of action in the prior four sessions

Training materials and content were adapted with peer navigators and based on formative qualitative findings to enhance relevance to urban refugee youth in Kampala. The WHO suggests making small changes to case examples such as relatable problems and social support–seeking examples. Peer navigators will deliver the five group sessions with groups of up to 20 participants.

We will provide participants in Arm 1 and Arm 2 with additional mHealth support, including SMS bidirectional check-ins, SMS mental health literacy messages, and supportive WhatsApp conversations. The aim of this mHealth support is to ensure that any participant in the VR/GMP+ group who needs additional mental health support or information will receive it, and that mHealth will also reinforce the information and access to resources shared in the intervention arms. The SMS program includes weekly SMS blasts designed to reinforce information provided in the VR on mental health literacy [18], psychological first-aid information and skills [34], and self-compassion activities [52]. There are also weekly bidirectional check-ins asking participants “how are you?” in their preferred language; any participant who responds they are not well or requests help will be referred within 48 hours to a social worker based at YARID as well as their peer navigator. This SMS platform is hosted by WelTel [53,54], a nonprofit agency [55]. The WelTel system will manage this bidirectional SMS intervention on their structured mobile phone platform on which all SMS interactions will be logged. To provide additional group-based support to participants, we will invite Arm 1 and Arm 2 participants to take part in weekly WhatsApp group discussions between peer navigators with ~25 participants assigned to each peer navigator. These discussions will be moderated by peer navigators, a research assistant, and a trained research coordinator, and will address the same content regarding mental health literacy, stigma, and stress-coping strategies covered in the VR intervention.

#### Arm 3: Waitlist Control

Participants in this arm will be waitlisted and receive the GPM+ intervention after implementation and follow-up. The waitlist control group will complete a fourth survey at 8 weeks to evaluate changes after participating in GPM+. In the meantime, the waitlist control group will have access to YARID resources and referrals as needed for mental health support.

### Outcomes

#### Primary Outcome

The primary outcome measured in this trial is *depression*, which will be measured using the Patient Health Questionnaire-9 [56].

#### Secondary Outcomes

Secondary outcomes include (1) *mental health literacy*, assessed with a modified depression literacy scale validated in LMICs [36-38]; (2) *attitudes toward mental health help–seeking*, assessed with the Inventory of Attitudes Towards Seeking Mental Health Services [57]; (3) *adaptive coping strategies*, assessed with the Kidcope [39] and Self-Compassion Scale for Youth [40]; (4) *mental health stigma*, measured using the Brief Version of the Internalized Stigma of Mental Illness scale [41]; (5) *mental well-being*, assessed with the WHO-Five Wellbeing Scale [42]; and (6) *level of functioning*, measured using the WHO Disability Assessment Schedule [43].

### Sample Size and Power Analysis

The study aims to include 330 participants, with 110 per study arm. Cluster sizes of 90 per group (n=270) are required to have 80% power (*P*<.05) to detect a difference of ~3 points in mean depression score (moderate effect size) at a level of significance of α=.05, assuming an intraclass correlation of 0.01 and SD of 7. With 10% attrition, 297 participants (99 per cluster) are required. Computations were performed using RStudio version 3.3.0, based on formulae for multiple comparisons of proportions and adjusted for design effect [58].

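### The stated inputs (3 points, SD 7, ICC 0.01, clusters of 90) give about 55% power at 90 per arm, not the stated 80%

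*Protocol article*

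**What the plan says.** The Sample Size and Power Analysis section of the protocol article prints all its inputs:

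- Size and power: "Cluster sizes of 90 per group (n=270) are required to have 80% power".
- Target: a difference of about 3 points in mean depression score, called moderate.
- Error rate: "at a level of significance of α=.05". Sidedness is not stated.
- Variability and clustering: "assuming an intraclass correlation of 0.01 and SD of 7".
- Method: "based on formulae for multiple comparisons of proportions and adjusted for design effect". The value of the design effect is not given.
- Attrition: "With 10% attrition, 297 participants (99 per cluster) are required".
- Enrolment: "The study aims to include 330 participants, with 110 per study arm".

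This section and Study Population and Eligibility Criteria use the same number per cluster as per arm, so the cluster is the arm. The abstract and Study Setting agree, with five settlements grouped into three sites. Study Design instead says that the five settlements are randomised 1:1:1 to the three arms.

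**The concern.** With whole sites as clusters, even an ICC of 0.01 nearly doubles the variance of an arm mean. A size of 90 that included this inflation should lie well above the individually randomised size for the same inputs. It lies only slightly above it.

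Depression is the only primary outcome, and the Discussion expects the findings to inform policy and scale-up. A reader told that the trial has 80% power for 3 points would take a null result as fair evidence against an effect of that size. On the printed inputs, the design would miss such an effect more than four times in ten.

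**Working it through.** **Inputs.** Difference d = 3, SD σ = 7, ICC ρ = 0.01, α = 0.05, power 80% and cluster size m = 90, all from Sample Size and Power Analysis. A two-sided test is assumed (z = 1.960 and 0.842). The calculations use the normal approximation and treat the ICC as known.

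**1. The printed figure, ignoring clustering.**
- n per arm = 2(1.960 + 0.842)²(7/3)² = 85.5, so 86.
- At n = 90, SE = √(2·49/90) = 1.044 and power = Φ(3/1.044 − 1.960) = 82%.

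Without a design effect, 90 per arm therefore meets the stated 80%.

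**2. With the stated ICC and one cluster per arm.** DE = 1 + (m − 1)ρ, SE = √(2σ²·DE/n), power = Φ(d/SE − 1.960), and the difference detectable with 80% power is 2.802·SE.

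| n per arm (= m) | DE | SE | Power for 3 points | Detectable at 80% |
|---|---|---|---|---|
| 90 | 1.89 | 1.435 | 55% | 4.0 |
| 99 | 1.98 | 1.400 | 57% | 3.9 |
| 110 | 2.09 | 1.364 | 59% | 3.8 |

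At 90 per arm the effective size is 90/1.89 = 47.6. For 90 to give 80% power, the ICC could be at most (90/85.47 − 1)/89 ≈ 0.0006.

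**3. If the five settlements are the clusters.** Under the grouping in Study Setting the arms hold 2, 2 and 1 settlements. An arm with two has m = 45 and DE = 1 + 44·0.01 = 1.44.
- Two versus two: SE = √(2·49·1.44/90) = 1.252, power 67%.
- Two versus one: SE = √(49·1.44/90 + 49·1.89/90) = 1.346, power 61%.

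**4. Omnibus test.** The Data Analysis Plan starts with an overall F test. With arm means 0, 3, 3 and DE 1.89, its power at 90 per arm is about 57%.

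**5. Baseline adjustment.** The Data Analysis Plan adjusts for the baseline outcome but gives no correlation r, so values of 0.5 and 0.7 are assumed. At 90 per arm, with between-site variance 0.01·49 = 0.49 and within-site variance 0.99·49 = 48.51:
- Adjustment reduces within-site variance only: SE = √(2[0.49 + 48.51(1 − r²)/90]). Power is 61% at r = 0.5 and 68% at r = 0.7.
- Adjustment reduces both components by (1 − r²): SE = 1.435·√(1 − r²). Power is 68% at r = 0.5 and 83% at r = 0.7.

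**6. Attrition.** 270 × 1.10 = 297. Keeping 270 after a 10% loss needs 270/0.90 = 300, or 100 per arm. The planned 110 per arm leaves 110 × 0.90 = 99.

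**The case against.** **A design-effect-adjusted route to 90 exists.** A difference of 0.5 SD (3.5 points) with two settlements of 45 per arm gives 2(2.802)²(7/3.5)² = 62.8, and 62.8 × 1.44 = 90.4. That fits the words about a moderate effect and a design effect. It does not fit a target of about 3 points or clusters of 90. This stands as a limit: a reader might infer that the authors forgot the design effect, since 86 is close to 90, but the document does not show it. The shortfall does not depend on how the 90 arose.

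**Baseline adjustment might restore the power.** A reader might infer that it cannot. The document does not support that: at an assumed r of 0.7, with both variance components reduced, power at 90 passes 80%. Equally, the power paragraph invokes no such adjustment and gives no correlation, so this cannot justify the printed figure.

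**Other conventions.** A one-sided test gives 67% with clusters of 90 and 77% with two settlements per arm. Only a one-sided test with clusters of 20 to 25 passes 80% (83% to 84%). Those are the sizes of the intervention and chat groups, not of the randomised units. Splitting α for multiple comparisons lowers power further.

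**The harm is limited.** Results will carry 95% CIs, which show precision directly, and baseline, intervention and first follow-up were already complete. Both points are fair, and they are why nothing beyond a restatement is asked. An interval is a full safeguard, however, only if it contains the between-site variance, which one site per arm cannot supply.

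**Side points.** The attrition slip has no practical effect, and the mention of proportions may only describe the cited reference. Both are wording corrections.

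**Conclusion.** The stated power does not follow from the stated inputs. With sites as clusters, two-sided power for 3 points is about 55% at 90 per arm, 57% at 99 and 59% at 110. With settlements as clusters it is about 61% to 67% at 90. Before baseline adjustment, no two-sided comparison of two arms that differ by 3 points reaches 80% at 90 per arm with either unit.

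These figures assume a two-sided test, the normal approximation and an ICC of exactly 0.01. They should not be read as the trial's true power. Baseline adjustment could raise power at 90 to between about 61% and 83% under assumed correlations of 0.5 to 0.7. In the other direction, one site per arm leaves no between-site degrees of freedom for the treatment contrast, which the normal approximation ignores, so the 55% to 59% are optimistic for an unadjusted comparison.

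**What to change.** First, state consistently in the abstract, Study Design, Study Setting and the power section whether three sites or five settlements are the randomised unit.

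Then restate Sample Size and Power Analysis, leaving enrolment at 330:

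- For one site per arm, SD 7 and ICC 0.01, 99 completers per arm give about 57% two-sided power for 3 points, or 80% power for about 3.9 points.
- Say that this is before baseline adjustment, is conditional on the assumed ICC, and is optimistic because the trial cannot estimate between-site variance with one site per arm.
- If settlements prove to be the unit, recompute with the actual 2, 2, 1 split.
- Describe the method as a comparison of two means with the design effect, and print that design effect.
- Give the size allowing for 10% attrition as 300 (100 per arm). This does not affect the 330 enrolled.

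The cost is one rewritten paragraph, consistent wording of the randomised unit elsewhere, and a less favourable stated power. Recruitment and analysis are unchanged.
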